**Methods:**

In this randomized waitlist controlled trial, cancer survivors experiencing anxiety- or cancer-related neuropathy (200 for neuropathy and 200 for anxiety) and who had finished primary cancer treatment were invited to participate. Data were collected at 3 time points regardless of randomization condition: baseline, 8 weeks, and 16 weeks. Both face-to-face and web-based recruitment strategies were used. The trial was opened for 2 separate primary outcomes (anxiety- or cancer-related neuropathy). The goal was not to compare these groups but to compare treatment and waitlist groups for each condition. In addition to evaluating the impact of mobile mindfulness on reported anxiety- or cancer-related neuropathy, other pain, fatigue, trauma, sleep, and satisfaction with the Mindfulness Coach app will also be assessed.

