## Methods

### Study Design

The study is being conducted with a randomized waitlist control design, such that participants were randomized through Qualtrics to either begin the intervention immediately or after 8 weeks. In addition, participants were invited to participate with the goal of impacting anxiety- or cancer-related neuropathy as a primary outcome (additional discussion on this below). The goal was to have 200 people complete the 8-week survey measures in each group. Funding was originally garnered to examine anxiety as a primary outcome, with additional seed funding received through the University of Hawai’i Cancer Center to test the same design for cancer-related neuropathy. These groups will not be compared with each other, rather, each treatment group (anxiety- and cancer-related neuropathy, respectively) will be compared with each waitlist control group (anxiety- and cancer-related neuropathy).

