#### Participants

Cancer survivors experiencing anxiety- or cancer-related neuropathy who had finished primary treatment for cancer were invited to participate in the study. They were first screened and then consented via Qualtrics, where all data were collected, as well. Inclusion criteria were the same for both groups, aside from the different scales used to measure levels of anxiety or neuropathy. Inclusion criteria for both groups include a previous diagnosis of cancer, other than nonmelanoma skin cancer; completion of primary treatment for cancer; not currently practicing meditation for more than 1 hour per week; age older than 21 years; comfortable reading and writing in English; routine access to the internet; and own a smartphone or tablet. There are no exclusion criteria.

For the anxiety group, participants needed to be experiencing cancer-related anxiety, per self-report, as indicated by a score of 22 or higher on the PROMIS (Patient Reported Outcomes Measurement Information System) anxiety short form measure [32]. For the neuropathy group, participants needed to be experiencing CIPN, per self-report, as indicated by a score of 22 points or higher on the Functional Assessment of Cancer Therapy-Cognitive subscale (FACT-GOG-Ntx) CIPN items [33]. The study was powered to examine differences between groups with 200 people in each group (200 total for anxiety, 200 total for neuropathy).

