## Results

### Overview

We will conduct the primary evaluation of the intervention, comparing changes in multiple outcomes between the treatment and waitlist control groups. Participants were randomized using a simple, open-label (nonblinded) randomization procedure. The intervention was individually guided and conducted electronically. We will follow an intent-to-treat approach, in which individuals are analyzed based on their randomization groups, regardless of adherence. Adherence effects will be examined in a subsequent analysis.

To account for repeated measures, we will run a mixed (both between- and within-subjects variables) linear or logistic model for each outcome. The independent variables are the randomization group (treatment vs waitlist control), time (baseline, 8 weeks, or 16 weeks), and the group by time interaction. The interaction term tests the intervention effect. For all analyses, the assumptions of the models will be checked and remedial measures (eg, transformations and nonparametric tests) will be taken as needed. Logistic models will assess dichotomous outcomes and linear models will assess continuous outcomes. Potential confounders (adherence, age, sex, and race or ethnicity) will be included. Where possible we will run the analyses within subgroups defined by these covariates, providing information on whether the intervention was more effective in certain groups (moderator effects). If there is evidence of nonrandom missing data, such as by differential dropout between groups, we will apply multiple imputation procedures. SAS (version 9.4; SAS Institute Inc) will be used to perform all analyses.

Data collection began in 2019 and was completed in 2023. We had very differential rates of recruitment for the differing arms with reaching near the target for the anxiety arm yet not for the cancer related neuropathy arm. This, along with other outcomes of the study will be reported in a separate manuscript.

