### Power

Assuming a Bonferroni corrected (for 10 outcome measures) 2-tailed type I error rate (α) equal to .005 (0.05/10), 80% power, and 200 participants per group (400 total), a standardized difference (Cohen *d* effect size) of 0.37 will be detectable. Cohen *d* is the standardized difference and can be converted to the original units by multiplying the SD of the original variable.

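### The power statement assumes 200 per arm, but each condition has 200 in total (about 100 per arm), so d = 0.37 at 80% power is not what either comparison can detect

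*Protocol article*

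**What the plan says.** The Power section of the protocol article gives one calculation for the whole study. It sets a "2-tailed type I error rate (α) equal to .005 (0.05/10") for ten outcome measures, takes "80% power, and 200 participants per group (400 total), a standardized difference", and concludes that a Cohen "effect size) of 0.37 will be detectable".

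Other sections describe a different comparison:

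- Participants: "The study was powered to examine differences between groups with 200 people in each group (200 total for anxiety, 200 total for neuropathy"). Here a group is a condition, and 200 is the total for that condition.
- Abstract, Methods: "The goal was not to compare these groups but to compare treatment and waitlist groups for each condition".
- Study Design: "The goal was to have 200 people complete the 8-week survey measures in each group". The same paragraph says that the two conditions are not to be set against each other.
- Results, Overview: recruitment ended up "reaching near the target for the anxiety arm yet not for the cancer related neuropathy arm".

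**The concern.** A detectable effect belongs to a particular contrast and to the number of people in each arm of it. The contrasts here are treatment versus waitlist among anxiety participants and treatment versus waitlist among neuropathy participants. Each draws on 200 people before randomisation splits them. The Power section uses 200 for each side of one comparison. Its total of 400 equals the two conditions added together, yet no stated analysis pools them or compares one with the other. The calculation looks as if the two conditions had been put in the place of the two randomised arms. That explanation is inferred, but the mismatch in n does not depend on it.

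What is at stake is how a null result will be read. Against a claim that 0.37 is detectable with 80% power, a non-significant result looks like fair evidence against a moderate effect. If power at 0.37 is nearer 40%, such an effect would be missed more often than found. This is the article's only power statement, so the problem touches both primary comparisons.

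**Working it through.** **Inputs**

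- Two-sided alpha .005 (0.05/10), power 80%, stated d = 0.37, 200 per group and 400 in total: Power section.
- 200 in total per condition: Participants section and Abstract.
- Comparison of treatment with waitlist within each condition: Abstract and Study Design.
- Allocation ratio: not stated (the Overview says only that randomisation was simple). I assume 1:1, so 100 per arm.

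**Formula.** For two means with SD = 1 and n per arm, detectable d = (z for 1 − alpha/2 + z for power) × √(2/n). With alpha .005 and 80% power, the z sum is 2.807 + 0.842 = 3.649. Each result was also checked with the noncentral t.

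**Step 1: reproduce the published figure, n = 200 per arm.**

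- d = 3.649 × √(2/200) = 3.649 × 0.1 = 0.365 (t: 0.367), which rounds to 0.37.
- Power at d = 0.37 is 81.4% (t: 80.9%).
- In reverse, n = 2 × (3.649/0.37)² = 195 per arm (t: 197).

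The published figure therefore comes from a plain two-sample calculation with 200 in each arm.

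**Step 2: the planned comparison, n = 100 per arm.**

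- d = 3.649 × √(2/100) = 3.649 × 0.1414 = 0.516 (t: 0.521).
- Power at d = 0.37: 0.37/0.1414 = 2.616, and 2.616 − 2.807 = −0.191, giving 42.4% (t: 41.4%).

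Halving n multiplies the detectable difference by √2.

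**Step 3: could another reading of the design recover 0.37 with 100 per arm?**

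| Variant | Detectable d (normal) |
|---|---|
| One-sided .005 | 0.483 |
| Two-sided .05, no Bonferroni | 0.396 (t: 0.398); power at 0.37 is 74% |
| Baseline-adjusted, r = 0.5 | 0.447 |
| Baseline-adjusted, r = 0.6 | 0.413 |
| Baseline-adjusted, r = 0.7 | 0.368 |
| Change score, r = 0.5 | 0.516 |
| Change score, r = 0.7 | 0.400 |

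The adjusted rows multiply 0.516 by √(1 − r²), and the change-score rows multiply it by √(2(1 − r)), where r is the correlation between baseline and follow-up. The article gives no r.

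**Step 4: neuropathy.** The number randomised is not given. As illustrations only (noncentral t, alpha .005), 50 per arm gives a detectable d of 0.75 and 16% power at 0.37. With 25 per arm these become 1.08 and 6%.

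**The case against.** Four points can fairly be made for the plan.

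1. The arithmetic is right for the inputs it names; the fault is in the input. This is true. The published result is still not the detectable effect of any comparison the trial makes.
2. The planned analysis is a repeated-measures mixed model, not a two-sample test at one time point, so 0.52 and 41% may understate its power. This stands as a limit on the size of the error: at r = 0.7 with baseline adjustment the detectable difference is back to 0.37. But the article states no correlation, its own figure already follows from the unadjusted formula with 200 per arm, and at r = 0.5 or 0.6 the claim still fails.
3. The figure of 400 may have another origin. The paragraph could remain from a single-condition plan with 200 in each arm, or it could pool both conditions into about 200 treated and 200 waitlisted. The text cannot settle which. None of these matches the stated design of 200 per condition with separate comparisons.
4. A power paragraph records planning, so it need not follow achieved recruitment, and the article openly reports the neuropathy shortfall. This is fair. The shortfall adds to the problem but does not create it, and the sizes in Step 4 are hypothetical.

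It could also be said that correcting the paragraph changes no estimate or test. That is so, but the paragraph is what readers will use to interpret a null finding.

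**Conclusion.** The concern holds. The Power section uses twice the number per arm that the Abstract and the Participants section allow for each condition. On the basis that yields the published 0.37, each planned comparison can detect about 0.52 with 80% power at two-sided .005, and has about 41% power at 0.37. A true effect of 0.37 would be missed about 59% of the time.

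These figures assume 1:1 allocation, all 200 participants per condition contributing outcome data, and no gain from baseline adjustment. Unequal allocation or missing data would enlarge the detectable difference. Adjustment would reduce it, reaching 0.37 only near r = 0.7. For neuropathy the detectable difference is larger again, by an amount that cannot be computed without the number randomised.

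**What to change.** Replace the Power paragraph with one statement per condition:

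- **Anxiety:** 200 in total, about 100 per arm; detectable d about 0.52 at two-sided .005 with 80% power. The uncorrected figure of about 0.40 at .05 may be given beside it if clearly labelled. If the authors wish to claim the gain from the mixed model, they should state the assumed correlation and its source, and show a range.
- **Neuropathy:** the same calculation at the number actually randomised. State that the effect will be reported as an estimate with a confidence interval, and that a non-significant result will not be read as absence of effect.

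Use the word group for one thing only, either condition or randomised arm, in the Power, Participants and Study Design sections, and give the allocation ratio.

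The cost is a text correction. Recruitment has closed and no further enrolment is proposed. The stated detectable effect becomes less favourable; the planned analyses do not change.

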## Discussion

We hope that this study will result in findings that are useful to improving the well-being of cancer survivors experiencing anxiety- and cancer-related neuropathy. If the study shows improvement in symptoms of anxiety or neuropathy in cancer survivors, it will allow for greater accessibility to mindfulness meditation via Mindfulness Coach, which is free, publicly available, and easily accessible through a mobile app. This will allow patients with cancer to access guided mindfulness meditation exercises in the comfort of their own homes and on their own time. This can be helpful for patients who may be too ill, lack resources, or live in a rural area where accessing a face-to-face mindfulness meditation intervention would be difficult or impossible. Results of the study may also be useful for clinicians working alongside patients with cancer or survivors searching for evidence-based, nonpharmacologic interventions to improve anxiety or neuropathy, with mindfulness meditation used alone or along with pharmacologic interventions.

Nonpharmacologic interventions, including exercise, yoga, and mindfulness meditation, have been studied for the treatment of psychological disorders, including anxiety, as a monotherapy or adjunctive therapy [41]. Current evidence supports the use of mindfulness meditation as an adjunctive therapy for people with an anxiety disorder, as there is limited evidence for mindfulness being used as a monotherapy for anxiety [41]. The general health benefits and low risk for harm justify the use of mindfulness as adjunctive therapy for patients with anxiety disorders and other mental health conditions such as depression [41]. At the current time, pharmacologic interventions for neuropathy are not highly effective and are not well tolerated by many patients due to various side effects [42,43]. First-line drugs used to treat neuropathy include antidepressants and anticonvulsants acting at voltage-gated calcium channels, which can have side effects including risk for cardiotoxicity, orthostatic hypotension, dry mouth, nausea, and confusion, among others [43]. In a randomized controlled trial involving 402 patients with neuropathy, 4 drugs commonly used for neuropathy of different drug classes (pregabalin, duloxetine, nortriptyline, and mexiletine) were tested for tolerance and treatment of neuropathic pain. The results of the study found that none of the drugs tested was clearly superior in performance or highly effective for treating neuropathic pain [42]. If results from this study show potential for mindfulness to be used as an alternative intervention to treat neuropathy, a larger number of people, including cancer survivors affected by CIPN, can access effective treatment without the side effects associated with medications commonly used to treat neuropathy.

Mobile apps have large dissemination potential and identifying apps that are found to be related to outcomes of interest is important given the ubiquitous nature of apps. Without identifying apps that are effective, apps that are available yet not effective can easily be reached. Findings from the currently described study will be published as soon as available.

## Abbreviations

CIPN: chemotherapy-induced peripheral neuropathy
FACT: Functional Assessment of Cancer Therapy
FACT-GOG-Ntx: Functional Assessment of Cancer Therapy-Cognitive subscale
FFMQ-SF: Five-Facet Mindfulness Questionnaire Short Form
MBSR: mindfulness-based stress reduction
MPQ: McGill Pain Questionnaire
PROMIS: Patient Reported Outcomes Measurement Information System
PTSD: posttraumatic stress disorder
UH: University of Hawai’i
